*Hypothesis 1*: the study groups receiving messages that focus on self-monitoring of outcomes of meditation behavior will have greater adherence to the ≥10 minute-per-day meditation prescription during the 8-week intervention and during the 8-week postintervention observation periods than the study groups receiving messages that focus on self-monitoring of meditation behavior.

In addition to self-monitoring messages, offering financial or in-kind incentives may be a successful strategy to further increase anchoring plan adherence [98]. Research from the behavioral economics literature suggests that traditional external rewards are often successful in *initiating* a wide range of health behaviors [99-101]. While the effects of these behavioral economics–based incentives often disappear once the incentives are withdrawn [21,23], it is possible that combining incentives with the anchoring strategy may leverage the short-term effectiveness of incentives to increase anchoring plan adherence and establish long-term habits [24]. One way in which this combined approach could be implemented is by using “time-contingent” incentives that are conditional on performing the target behavior at approximately the same time that the planned anchor (ie, existing routine) is expected to occur. Such time-contingent incentives (TCIs) may direct participants’ focus and attention to the use of their anchors, which may help to better maintain meditation after the incentives are withdrawn. To test this approach and compare these strategies with the previous behavioral economics literature, the intervention study groups will receive either TCIs or non-TCIs (NTCIs) during the 8-week intervention period. This variation in intervention approaches will allow us to evaluate the following hypothesis:

*Hypothesis 2*: The study groups receiving TCIs will have greater adherence to their anchoring plans and to the ≥10 minute-per-day meditation prescription during the 8-week intervention and during the 8-week postintervention observation periods than the study groups receiving NTCIs.

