### Study Design

This study will use a 5-arm, parallel, partially blinded (participants only) randomized controlled design. After completing a web-based eligibility survey, the participants will be randomized into 1 of the 5 study groups. Stratified randomization methods will be used to ensure that race and ethnicity (ie, Hispanic) are equally represented across study groups. The 5 study groups include a control group that will use the anchoring plan to form a meditation habit with Calm and then receive no additional intervention supports, while the 4 intervention groups will also use the anchoring plan in combination with 1 of the 2 different types of self-monitoring messages and 1 of the 2 different forms of incentives. Participants in the 4 intervention groups will also be eligible for an in-kind reward (eg, Calm t-shirt, Calm tote bag, or Calm water bottle; all gifts have a retail value of roughly US $25 but a wholesale cost of US $5) conditional on either completing ≥10 minutes of meditation at any time of day on at least 8 days over a 2-week period (NTCIs) or completing ≥10 minutes of meditation within a 2-hour window around the time their chosen anchor typically occurs during the day (ie, anchor time1 hour) on at least 8 days over a 2-week period (TCIs). All additional interventions to support adherence to the anchoring plan will be delivered for 8 weeks; thus, participants are eligible to win up to 4 in-kind incentives during the intervention period. Participants within the intervention groups will also be randomly assigned to receive either messages that focus on self-monitoring of behavior (eg, “You completed a meditation session using your Calm app on at least 8 days during the past 2 weeks”) or messages that focus on self-monitoring of outcomes of behavior (eg, “We encourage you to continue using the ‘How Are You Feeling?’ check-in feature after completing your meditation sessions”). The “How Are You Feeling?” check-in feature is an existing feature available to all users of the Calm app that allows users to record their current mood state (eg, happy, sad, or anxious). The fractional factorial study design is shown in Table 1.

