### Sample Size

The target recruitment sample size for this study is 555 participants, with 111 participants per study group. On the basis of our existing studies using the Calm app, we anticipate a 20% study attrition, which will yield an effective study group sample size of 88. Our primary measure of meditation app adherence is a binary indicator variable for performing ≥10 minutes of meditation on at least 4 days of the week. This measure of adherence is based on the concept of behavioral regularity, which was proposed by Cheung et al [102] as a standardized measure of treatment adherence. In addition, researchers have recommended that practicing mindfulness for 3 to 4 days per week is the sufficient level of adherence (or regularity) for attaining the mental health benefits associated with meditation, such as stress reductions [103], and this recommendation is theoretically consistent with the notion that a mindful mind is the product of frequent, effortful, and persistent training [104,105]. Thus, we determined our sample size to detect study group differences in meditation regularity at the end of the study (week 16). Using data from our previous studies with Calm, we know that approximately 15% of new Calm users regularly meditate (ie, complete ≥10 minutes of meditation for at least 4 days of the week) 8 weeks after first subscribing to the app and fewer than 10% regularly meditate with Calm 16 weeks after subscribing. An effective study group sample size of 88 provides adequate statistical power (1–β=.82) for detecting study group differences of 18 percentage points in the likelihood of regular mediation in week 16 (Cohen *h*=0.43, which is a small to medium effect size).

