where *y_i_* is a binary variable equal to 1 if individual i completed ≥10 minutes of meditation for ≥4 days during week 8 of the study; T1 is an indicator for treatment group 1 (that receives self-monitoring behavior messages and NTCIs); T2 is an indicator for treatment group 2 (that receives self-monitoring outcome messages and NTCIs); T3 is an indicator for treatment group 3 (that receives self-monitoring behavior messages and TCIs); T4 is an indicator for treatment group 4 (that receives self-monitoring outcome messages and TCIs); and *ϵ_i_* is the idiosyncratic error. The coefficients of interest are *β*_1_ through *β*_2_. Equation 2 has the term *X_i_β*_5_, which includes a vector of the following observable participant characteristics (*X_i_*): age, education, sex, race, ethnicity, household income, self-reported mental and physical health, baseline meditation habit strength, intrinsic motivation for meditation, and measures of time and risk preferences and the respective coefficients (*β*_5_). For more information on our data analysis plan, please see Multimedia Appendix 1.

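### The coefficients named as of interest are arm-versus-control effects, which are not the comparisons in Hypotheses 1 and 2, although the stated model can estimate both

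*Protocol article*

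**What the plan says.** **Hypotheses (Introduction, Habits as a Key Strategy to Maintain Adherence).** Hypothesis 1 is that "the study groups receiving messages that focus on self-monitoring of outcomes of meditation behavior will have greater adherence" "than the study groups receiving messages that focus on self-monitoring of meditation behavior". Hypothesis 2 is: "The study groups receiving TCIs will have greater adherence to their anchoring plans and to the ≥10 minute-per-day meditation prescription", compared with the NTCI groups. Both are stated for the intervention period and for the postintervention period.

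**Design (Study Design, Table 1).** "The fractional factorial study design is shown in Table 1". The table gives a control arm and a 2×2 of message type by incentive type:

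- T1: behavior messages, NTCI
- T2: outcome messages, NTCI
- T3: behavior messages, TCI
- T4: outcome messages, TCI

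**Model (Data Analysis Plan, Equations 1 and 2).** The main unadjusted and adjusted logistic models contain one indicator for each treated arm, with control as the reference. The target is then stated: "The coefficients of interest are *β*_1_ through *β*_2".

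**Sample Size.** "An effective study group sample size of 88 provides adequate statistical power" (0.82) for an 18-point difference between study groups in week 16, with Cohen h = 0.43.

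**The concern.** When an article names its coefficients of interest, it tells the reader which estimates decide its hypotheses. Here those estimates and the hypotheses do not match. As printed, the sentence leaves out both TCI arms, so one side of Hypothesis 2 is missing, as is half of each side of Hypothesis 1. Extending it to β4 adds the missing arms but still names only differences from control. Two arms can each differ from control without differing from each other, so a set of arm-versus-control results does not settle either hypothesis.

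Two of the three hypotheses therefore have no stated estimand in the article's main models. The comparison that decides them could be chosen after the data are seen: one arm pair, both pairs separately, or the pooled contrast. These choices also differ in precision, because the pooled contrast uses twice as many participants per side as a single pair.

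**Working it through.** **1. What each coefficient is.** With control as reference, β_k is the log-odds of regular meditation in arm k minus that in control, for k = 1 to 4.

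**2. What the hypotheses require**, using the arm definitions in Table 1:

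- Hypothesis 1 (T2, T4 vs T1, T3): (β2+β4)/2 − (β1+β3)/2
- Hypothesis 2 (T3, T4 vs T1, T2): (β3+β4)/2 − (β1+β2)/2

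Control cancels from both. Neither expression is a single β, and neither can be formed from β1 and β2 alone. Both can be formed from β1 to β4, so Equations 1 and 2 identify them.

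**3. Whether the article states them elsewhere.** In the Data Analysis Plan, the analysis of covariance, the McNemar test and the mixed model refer only to group-level or study-group differences. The moderation and mediation paragraph uses the same arm indicators. The limitations paragraph of the Discussion compares the NTCI and TCI groups with control. None gives a contrast between message types or between incentive types.

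**4. The plan's own power figure.** Inputs from Sample Size: 88 per group (111 × 0.8 = 88.8), h = 0.43, power 0.82. Alpha is not stated, so two-sided 0.05 is assumed.

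- Power = Φ(h·√(n/2) − 1.96)
- n = 88: Φ(0.43 × 6.633 − 1.96) = Φ(0.892) = 0.81, against 0.82 stated, so the figure is reproduced.
- 15% vs 33% gives h = 0.4285, and 10% vs 28% gives h = 0.4717. The stated h thus fits a 15% reference. The article gives about 15% at week 8 and below 10% at week 16, so both are shown below.

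The stated power is therefore for one arm against one other arm.

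**5. The same calculation for the factor-level comparisons.** Each side pools two arms: 2 × 88 = 176.

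- Power at h = 0.43: Φ(0.43 × 9.381 − 1.96) = Φ(2.074) = 0.98
- Smallest h at 82% power, (1.960 + 0.915)/√(n/2): 0.433 for n = 88 and 0.307 for n = 176

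| Reference rate | Detectable, 88 vs 88 | Detectable, 176 vs 176 |
|---|---|---|
| 15% | 18.2 points | 12.4 points |
| 10% | 16.3 points | 10.9 points |

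These use the arcsine scale. A pooled-variance formula gives 18.5 and 12.5 points from 15%, and 16.7 and 11.1 from 10%, so the conclusion is the same.

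**6. Whether the article's own model delivers this precision.** On a linear scale with unit variance, the standard error is √(2/88) = 0.151 for one pair and √(1/88) = 0.107 for the contrast, a ratio of 1.41. As a check on the logistic scale, 2,000 trials were simulated per scenario with 88 per arm, control at 10% and no interaction. For TCI 33% vs NTCI 15%, the contrast of the β's had power 0.98, against 0.83 for one arm pair. For 27.6% vs 15% the figures were 0.82 and 0.55. No change to the model is needed to gain the pooled precision.

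**The case against.** The case on the other side has real substance.

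- **A reader might infer that the trial cannot test Hypotheses 1 and 2, or never will.** The article does not support that. It states both comparisons in words, and its model estimates all four arms, so both contrasts are available after fitting. It also refers to Multimedia Appendix 1 for more on the analysis, and contrasts are the kind of detail such an appendix may hold. This objection stands. What remains is that the article chose to state its coefficients of interest, and that statement does not match the hypotheses whatever the appendix says.
- **The β2 is probably a typographical slip.** The same equations print T where T1 is meant and leave parentheses open, and all four indicators are defined. This is accepted. Correcting the slip still leaves only comparisons with control.
- **A reader might infer that the sample size is wrong or that factorial pooling has been given up.** Neither follows. The power figure is correct for a pairwise comparison and conservative for the pooled contrasts, and nothing in the article excludes pooling.
- **Comparisons with control have their own purpose.** The study aims speak of study-group differences, and the Discussion plans to compare the incentive groups with control. This stands, so there is no reason to demote those effects.
- **A reader might also infer that the hypotheses will be judged by which arms reach significance against control, with false differences as a result.** The article states no such rule, so error rates built on it carry no weight here.

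**Conclusion.** The point holds as a mismatch between the stated target and the hypotheses. The coefficients named as of interest, whether read as β1 to β2 or as β1 to β4, are arm-versus-control effects. Hypotheses 1 and 2 are comparisons among the treated arms, and the article states no contrast for either. The model, the design and the pairwise power figure are not at fault.

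At 82% power, naming the pooled contrasts lowers the detectable difference from 18.2 to 12.4 points at a 15% reference, or from 16.3 to 10.9 at 10%. This assumes two-sided 0.05 with no multiplicity adjustment, 88 per arm retained, and no strong message-by-incentive interaction. The mismatch itself depends on none of these assumptions. Whether the contrasts are already written in Multimedia Appendix 1 cannot be settled from the article.

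**What to change.** 1. Correct the sentence on the coefficients of interest to β1 through β4.
2. Name (β2+β4)/2 − (β1+β3)/2 as the test of Hypothesis 1 and (β3+β4)/2 − (β1+β2)/2 as the test of Hypothesis 2.
3. Say which outcomes and weeks they apply to. At weeks 8 and 16, Hypothesis 1 covers meditation adherence (2 tests), and Hypothesis 2 covers meditation and anchoring adherence (4 tests), 6 in all. The text under the equations defines y only for meditation in week 8, so it should be extended to match.
4. State which outcome and week is confirmatory before applying any multiplicity control to the two contrasts. Without that, an adjustment for two tests does not say which two.
5. Report the message-by-incentive interaction, (β4−β3) − (β2−β1), alongside.
6. Keep the arm-versus-control effects for the aims of comparing study groups and comparing the incentive groups with control.
7. Optionally, add the 176 vs 176 detectable differences to Sample Size, with their assumptions. The existing 88 vs 88 figure can stay.

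If Multimedia Appendix 1 already gives the contrasts, items 2 to 5 reduce to a cross-reference and a check that the two texts agree.

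The cost is a few sentences and post-estimation linear combinations in Stata. Design, recruitment, data collection and model do not change. The one downside is that, if the two factors interact, each pooled contrast is an average over the levels of the other factor. That is why the interaction should be shown with it.

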### Data Analysis Plan

To examine our specific aims, statistical analyses comparing group-level differences in the primary and secondary outcome measures will be performed. First, an analysis of covariance framework will be used to test for group-level differences in each primary and secondary outcome, controlling for participant characteristics that are found to significantly differ between study groups at baseline. For analyses of dichotomous outcomes, such as meditation regularity at weeks 8 and 16, a nonparametric McNemar test and multiple logistic regression that controls for additional participant-level covariates will be used to assess study group differences. In addition to static comparisons of group means for each outcome, the longitudinal nature of the app use data will be leveraged by using repeated measures and time-series techniques. Specifically, a linear mixed model with repeated observations will be fitted using maximum likelihood through “xtmixed” in the software package Stata (StataCorp) to study group-level temporal dynamics in the primary and secondary outcomes.

To estimate the impact of our intervention on our static primary outcomes of meditation regularity and anchoring plan regularity at weeks 8 and 16, we will use logistic regressions with the following specifications.

Our main unadjusted model will have the following form:

Pr(y_i_) = exp(*β*_0_+ *β*_1_T + *β*_2_T2 + *β*_3_T3 + *β*_4_T4 + ε_i_  **(1)**

Our main adjusted model has the following form:

Pr(y_i_) = exp(*β*_0_+ *β*_1_T + *β*_2_T2 + *β*_3_T3 + *β*_4_T4 + X_i_
*β*_5_ + ε_i_  **(2)**

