In addition, we will investigate potential intervention moderators and mediators. Specifically, we will use the same regression models specified earlier in this section and include additional interaction terms between each study group indicator variable and a single moderating variable measured at baseline. Significant coefficients estimated for these interaction terms will be used to identify the moderating effects of participants’ baseline characteristics, such as age, gender, race, and employment information. In addition, we will separately examine the mediating effects of anchoring plan adherence and habit strength at the end of the intervention on the maintenance of mediation following the procedures outlined by Judd and Kenny [113]. We will first regress meditation measured in week 16 on indicator variables for each study group and then regress meditation in week 16 on indicator variables for each study group as well as anchoring plan adherence measured over the first 8 weeks (ie, during the intervention). The mediating effect of anchoring plan adherence (our third hypothesis) will be calculated by subtracting the coefficients estimated in the first regression from those in the second regression. We will also use these procedures to investigate the mediating effect of habit strength measured at week 8 (ie, immediately after the intervention). We will also use a modern mediation analysis technique that allows for additional covariates when estimating the direct and indirect treatment effects in the equations described earlier [114].

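### Moderators are identified from individual arm-by-covariate coefficients, at least four per moderator, where one joint test per moderator would hold the false-positive rate at 5%

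*Protocol article*

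**What the plan says.** The main models in the Data Analysis Plan section carry four arm indicators, T1 to T4, with the control group as reference. They are applied to "our static primary outcomes of meditation regularity and anchoring plan regularity at weeks 8 and 16".

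The moderator analysis is introduced with "In addition, we will investigate potential intervention moderators and mediators". It reuses those models and will "include additional interaction terms between each study group indicator variable and a single moderating variable measured at baseline". The decision rule follows: "Significant coefficients estimated for these interaction terms will be used to identify the moderating effects". The candidates are "participants’ baseline characteristics, such as age, gender, race, and employment information", which is an open list.

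The section as printed gives no significance level, no joint test of a moderator's interaction terms and no adjustment. It refers to Multimedia Appendix 1, which is not at hand, for more on the analysis plan.

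**The concern.** Whether a characteristic moderates the intervention is one question per characteristic. The printed rule answers it with at least four tests, which are correlated because every coefficient is a contrast with the same control group. A race or employment variable with several categories brings more: three categories give 2 x 4 = 8 coefficients.

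If one significant coefficient is enough to name a moderator, the chance of naming one wrongly exceeds the level of each test. At stake is how far a reported moderator can be believed. The comparisons between arms on the primary outcomes do not depend on this step.

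**Working it through.** **Inputs from the article.** There are five arms: "The target recruitment sample size for this study is 555 participants, with 111 participants per study group". On attrition, "we anticipate a 20% study attrition, which will yield an effective study group sample size of 88" (111 x 0.8 = 88.8). The Sample Size section gives an 18-point difference, Cohen h = 0.43 and power 0.82, with background rates of about 15% at week 8 and below 10% at week 16.

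**Assumptions.** Level 0.05 two-sided; any significant coefficient counts as moderation; four moderators with one term each, independent of one another; one outcome at one week.

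**The plan's own figure.** Power = Phi(h x sqrt(n/2) - 1.960) = Phi(0.43 x sqrt(44) - 1.960) = Phi(0.892) = 0.814, close to the stated 0.82. A one-sided level would give 0.886. The two-sided 0.05 assumption therefore fits the plan. An h of 0.43 corresponds to 15% against 33% (h = 0.428), called the design rates below.

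**One moderator, large-sample.** Each interaction estimate is an arm's slope minus the control slope. With equal slope variances V, two such estimates have covariance V and variance 2V each, so their correlation is 0.5. From 1,000,000 draws of four such z statistics with no true interaction:

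| Rule | False-positive rate |
|---|---|
| Any of four coefficients, correlation 0.5 | 15.5-15.6% |
| Same, correlation 0.6 | 14.4% |
| Same, correlation 0.7 | 13.0% |
| One joint 4-df test | 5.0% |

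The higher correlations are relevant because a control group with a lower event rate has a less precise slope.

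**Four moderators, large-sample.**
- Joint test for each: 1 - 0.95^4 = 18.5%.
- Any coefficient for each: 1 - (1 - 0.155)^4 = 49%.

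So testing four moderators takes 5% to 18.5%, and the coefficient rule takes 18.5% to 49%.

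**Simulated trials at the plan's size.** Logistic models with Wald tests and no true interaction, 88 or 111 per arm, one continuous and three binary moderators, 1,200 trials per scenario. The binary moderators were split either 50/50 or unevenly (80/20, 80/20, 65/35; assumed).

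| Rates (control, active arms) | At least one false moderator of four |
|---|---|
| 10%, 10% | 26-44% |
| 15%, 15% | 33-48% |
| 10%, 28% | 32-39% |
| 15%, 33% (design rates) | 37-45% |
| 33%, 33% | 46-50% |

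Per moderator, the continuous one gave 12-17% and the evenly split binary ones 9-16%. At the design rates, all types lay between 9% and 17%. Uneven binary moderators with rare outcomes fell lower, to about 2% for an 80/20 split at 10% in every arm. There the Wald test is conservative, and this produces the low end of the 26-50% range.

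With one joint Wald test per moderator in the same trials, the rate over all four was 5-18%. A Bonferroni step over the four (0.0125 each) brought it to 1-4%.

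**Price in power.** Large-sample check, correlation 0.5, each true interaction 2.8 standard errors (assumed):

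| True interaction | Any of four | Joint test |
|---|---|---|
| One arm only | 84% | 82% |
| Two arms, same direction | 93% | 95% |
| All four arms, same size | 97% | 82% |

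The two rules do not have the same size: the first runs at about 15.6% under the null, the second at 5%.

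**The case against.** **The article is condensed.** A level, a joint test, an adjustment and a closed list of moderators could all stand in Multimedia Appendix 1. This objection stands, and it limits any statement about a missing joint test to the text as printed. It does not remove the point, because the article states how moderators are identified, and that stated rule is what is at issue.

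**The wording does not say that any one coefficient suffices.** Each coefficient could be read as asking whether a covariate modifies one arm's effect against control, and each such test keeps its own level. That reading is possible, so the figures are conditional on the any-coefficient reading. The text does not restrict its conclusion to single arms.

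**The analysis is supplementary.** This is correct. Moderation appears in none of the three aims or three hypotheses, and the text speaks of potential moderators.

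**Stronger readings that the documents do not support.**
- A reader might infer that a fixed share of such trials, say 35-45%, would report a false moderator. That share depends on a level, a number of moderators and a coding that the article does not fix, and part of it comes from testing four characteristics at all.
- A reader might infer that false moderators would steer later targeting of the intervention. The article states no such use.
- A reader might infer that coefficients against control are an error because Hypotheses 1 and 2 compare message types and incentive types. The article does not promise to test moderation of those factors, and such contrasts are linear combinations of the four planned coefficients, so the model does not prevent them.

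**Conclusion.** The point holds for the rule as printed. Under a two-sided 0.05 level and the any-coefficient reading, the false-positive rate is about 10-16% per one-parameter moderator instead of 5%, with lower values for very uneven binary moderators and rare outcomes. Over the four named moderators, for one outcome at one week, it is about 26-50%, assuming one term each and independent covariates. Up to 18.5% would remain with joint tests, so not all of the excess belongs to the coefficient rule. More moderators, or counting both outcomes and both weeks, would raise the total.

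This is a worthwhile correction to a supplementary analysis. It gives no reason to doubt the primary arm comparisons.

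**What to change.** Decide each moderator by one joint test of all its arm-by-moderator interaction terms: 4 df for a binary or continuous moderator, more for one with several categories. Interpret individual coefficients only if the joint test is significant. Report the results as exploratory and state how many moderators were tested. A correction across moderators is optional in an exploratory analysis; without one, the number tested lets the reader judge the remaining error. If Multimedia Appendix 1 already specifies a joint test, align the Data Analysis Plan section with it.

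The cost is a change of wording, with no new data. There will be fewer nominal moderator findings, and some power is lost when the interaction is the same in all four arms (97% to 82% in the check above).

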#### Primary Outcomes: Adherence Maintenance (Objective App Use Data)

The primary outcomes for this study measure participants’ ability to maintain adherence to the ≥10 minute-per-day meditation prescription over the 16-week study period. Specifically, we will measure meditation adherence as a binary variable equal to 1 if participants complete ≥10 minutes of meditation for ≥4 days per week and 0 otherwise. This meditation adherence outcome will be defined weekly during both the 8-week intervention and the 8-week postintervention observation periods. We will also measure objective meditation app use using the number of days with ≥10 minutes of meditation per week and the total number of meditation minutes per week, both of which will allow us to investigate the behavioral frequency of app-based meditation and improve the statistical power of our analyses. We will also augment these objective app-based meditation measures with a self-reported measure of days with any meditation (ie, either using the app or meditation outside the app) over the past week that is assessed at baseline, week 8, and week 16 time points. We will measure anchoring plan adherence as a binary variable equal to 1 if participants complete ≥10 minutes of meditation within 1 hour of the timing of their chosen anchor for ≥4 days per week and 0 otherwise. Similar to overall meditation, we will also measure anchoring plan adherence as the number of days completing ≥10 minutes of meditation within 1 hour of the timing of their chosen anchor per week.

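### The mediating effect for Hypothesis 3 is defined as direct minus total, which reverses its sign; if the two regressions are logistic, the coefficient difference is also distorted by non-collapsibility.

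*Protocol article*

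**What the plan says.** The mediation paragraph of the protocol article's Data Analysis Plan fixes three steps.

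- Step 1: "We will first regress meditation measured in week 16 on indicator variables for each study group".
- Step 2: the same regression with an added term, "anchoring plan adherence measured over the first 8 weeks (ie, during the intervention").
- Step 3: the mediating effect, identified there as the third hypothesis, is "calculated by subtracting the coefficients estimated in the first regression from those in the second regression".

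The same procedure is then applied to habit strength at week 8. The paragraph ends with a second method: "We will also use a modern mediation analysis technique that allows for additional covariates when estimating the direct and indirect treatment effects".

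The paragraph names neither the link function nor the meditation measure for steps 1 and 2. Earlier in the section, for "meditation regularity and anchoring plan regularity at weeks 8 and 16, we will use logistic regressions with the following specifications", the models are logistic. The Primary Outcomes section makes the main measure binary ("we will measure meditation adherence as a binary variable equal to 1 if participants complete" the weekly threshold), and also defines days per week and "the total number of meditation minutes per week".

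**The concern.** Step 1 estimates each group's total effect on week-16 meditation. Step 2 estimates the direct effect, the part left after conditioning on anchoring adherence. The mediated part is what disappears between the two, so it is first minus second. The plan states the reverse.

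Hypothesis 3 predicts a positive relation: more anchoring during the intervention, better maintenance afterwards. Under the stated formula, support for the hypothesis would normally appear as a negative number, and a positive number could be misread as support.

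The second question is scale. Logit coefficients are non-collapsible: when there is a direct group effect, adding a variable that predicts the outcome enlarges the group coefficients even if the groups do not affect that variable. Anchoring adherence is built from days that are themselves qualifying meditation days, so it should predict later meditation. The difference between two logit coefficients then mixes the indirect effect with a change of scale.

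This calculation is the one the plan ties to Hypothesis 3 and hence to the third study aim.

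**Working it through.** The plan gives no figure for a mediating effect, so there is none to reproduce.

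**Sign.** Let c be the group coefficient in step 1 and c′ the coefficient in step 2. In a linear model c = c′ + indirect effect. The plan's quantity is c′ − c = −(indirect effect). This needs no assumption about effect size.

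**Scale, if the models are logistic.** Inputs from the Sample Size section: a week-16 regular-meditation rate below 10% in new users (10% used), a design difference of 18 percentage points (10% versus 28% used), and 88 per group. Everything about the mediator is assumed, because the documents give nothing: M is normal with SD 1, its mean is shifted by d in the treated group, and logit Pr(y=1) = a + c′T + bM. The intercept a is solved for a 10% control rate. The total log odds ratio c comes from averaging over M.

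*No mediation (d = 0), assumed direct log odds ratio c′ = 1.0:*

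| Mediator OR per SD | c | c′ − c (plan) | c − c′ (order corrected) | truth |
|---|---|---|---|---|
| 3 | 0.87 | +0.13 | −0.13 | 0 |
| 8 | 0.67 | +0.33 | −0.33 | 0 |

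*Total effect fixed at 10% versus 28%:* c = ln(0.28/0.72) − ln(0.10/0.90) = 1.253.

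| b | d | c′ | c′ − c (plan) | indirect risk difference |
|---|---|---|---|---|
| 1 | 0 | 1.431 | +0.18 | 0 |
| 2 | 0 | 1.878 | +0.63 | 0 |
| 2 | 0.2 | 1.478 | +0.23 | +4.8 points |
| 1 | 0.5 | 0.931 | −0.32 | +7.8 points |
| 2 | 0.5 | 0.878 | −0.38 | +11.1 points |

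A binary mediator (30% prevalence, no shift) gives the same pattern: +0.06 at odds ratio 3 and +0.28 at odds ratio 10.

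**Finite samples.** In 2,000 simulated pairs of arms with 88 each and no mediation, the plan's logistic difference averages +0.20 at b = 1 (above zero in 88% of runs) and +0.70 at b = 2 (98%). The linear-probability difference averages about zero (0.0006 and 0.0010).

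**Real mediation, and whether reversing the order is enough.** Take d = 0.5, mediator odds ratio 3 and direct log odds ratio 0.30. Then c = 0.74 and the plan returns 0.30 − 0.74 = −0.44. The reversed value, +0.44, is close to but below the natural indirect log odds ratio of 0.47.

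**Boundary case.** With no group effect at all (c′ = 0, d = 0), the difference is 0.

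**The case against.** Four points deserve weight.

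- **The logistic reading is an inference.** The mediation paragraph does not name a link or a measure, and days or minutes per week could be modelled linearly. The article refers to a fuller data analysis plan in an appendix that is not shown, and such detail may be there. This stands: the scale problem is conditional. The sign is not, because the order of subtraction is printed in the article and nothing else in it corrects it.
- **A second mediation method is planned.** It is a partial safeguard. But it is introduced as an addition, Hypothesis 3 is attached to the coefficient subtraction, and nothing says which result decides if the two disagree.
- **The sign can be recovered** from the two fitted models by any careful reader. True for a linear model. For a logistic model, reversing the order leaves the scale distortion in place.
- **The consequences are easy to overstate.** A reader might infer that the plan always shows mediation when there is none and always shows a negative value when mediation is real. Neither follows. A spurious value needs a direct group effect and a mediator that predicts the outcome; without any group effect the difference is 0. Weak real mediation through a strong mediator can still give a positive value under the plan's formula (+0.23 at b = 2, d = 0.2).

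**Conclusion.** The sign error holds outright: as written, the mediating effect is direct minus total, and in a linear model a true positive pathway is reported as negative. It applies to anchoring adherence and, by the same procedure, to habit strength.

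The scale error holds if the binary week-16 outcome is analysed with the section's logistic models, which is the natural reading but is not stated. Its size rests on assumed mediator strength and direct effect: +0.13 to +0.33 on the log-odds scale with no mediation, for a direct log odds ratio of 1.0 and mediator odds ratios of 3 to 8 per SD. It would be wrong to read these as false positives that survive a corrected order. Once the order is reversed they become −0.13 to −0.33, so mediation is understated, and a weak real pathway can be masked (−0.23 where the indirect risk difference is +4.8 points).

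The group comparisons for Hypotheses 1 and 2 and the sample size do not depend on this calculation.

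**What to change.** 1. Define the indirect effect as first minus second (total minus direct), for both anchoring adherence and habit strength.
2. Name the week-16 meditation measure and the model used in the mediation regressions.
3. For the binary outcome, drop the raw difference of logit coefficients. Make the direct/indirect-effect method already planned in the same paragraph the deciding analysis for Hypothesis 3, reported as a risk difference with a bootstrap confidence interval.
4. Keep a simple coefficient difference only for linear models of days or minutes per week.

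The cost is analysis-plan wording. No new data are needed, and the change should be made before the mediation analysis is run.
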